## Abstract

**Background:**

The brain is a common site for cancer metastases. In case of large and/or symptomatic brain metastases, neurosurgical resection is performed. Adjuvant radiotherapy is a standard procedure to minimize the risk of local recurrence and is increasingly performed as local stereotactic radiotherapy to the resection cavity. Both hypofractionated stereotactic radiotherapy (HFSRT) and single fraction stereotactic radiosurgery (SRS) can be applied in this case. Although adjuvant stereotactic radiotherapy to the resection cavity is widely used in clinical routine and recommended in international guidelines, the optimal fractionation scheme still remains unclear. The SATURNUS trial prospectively compares adjuvant HFSRT with SRS and seeks to detect the superiority of HFSRT over SRS in terms of local tumor control.

**Methods:**

In this single center two-armed randomized phase III trial, adjuvant radiotherapy to the resection cavity of brain metastases with HFSRT (6 – 7 × 5 Gy prescribed to the surrounding isodose) is compared to SRS (1 × 12–20 Gy prescribed to the surrounding isodose). Patients are randomized 1:1 into the two different treatment arms. The primary endpoint of the trial is local control at the resected site at 12 months. The trial is based on the hypothesis that HFSRT is superior to SRS in terms of local tumor control.

**Discussion:**

Although adjuvant stereotactic radiotherapy after resection of brain metastases is considered standard of care treatment, there is a need for further prospective research to determine the optimal fractionation scheme. To the best of our knowledge, the SATURNUS study is the only randomized phase III study comparing different regimes of postoperative stereotactic radiotherapy to the resection cavity adequately powered to detect the superiority of HFSRT regarding local control.

**Trial registration:**

The study was retrospectively registered with ClinicalTrials.gov, number NCT05160818, on December 16, 2021. The trial registry record is available on https://clinicaltrials.gov/study/NCT05160818. The presented protocol refers to version V1.3 from March 21, 2021.

## Background

Depending on the underlying tumor, up to 30 per cent of all cancer patients develop brain metastases in the course of their disease [1]. Without any treatment, the survival after diagnosis of symptomatic brain metastases is only about a few weeks to months [2, 3]. Since the risk of local recurrence is very high with resection alone [4], postoperative radiotherapy is recommended. However, there is controversy about the best treatment regimen. Many centers prefer adjuvant radiotherapy of the resection as local treatment over whole brain radiotherapy (WBRT) as a standard procedure, due to the superiority in terms of neurocognitive side effects and comparable survival [5].

Adjuvant local irradiation is well established in the context of limited brain metastases [5–8], yet data regarding extensive brain disease (> 4 metastases) is emerging [9–11]. Its use is more frequently recommended in international guidelines such as the NCCN National Comprehensive Cancer Network® Guideline Central Nervous System Cancers V1.2022. Despite intensive research, the optimal dose prescription of adjuvant radiotherapy to the resection cavity remains unclear. The resection cavity can be treated in few fractions (hypofractionated stereotactic radiotherapy, HFSRT), or with single dose radiosurgery (SRS). Both regimen are used in clinical routine, and every center may have their preference, or apply both, depending on cavity volume, location, or other patient-related factors. When determining the dose, a balance must be struck between tumor control and the risk of radionecrosis in particular. Data available on radiotherapy of the resection cavity is mostly retrospective in nature. There exist only two recent prospective adequately powered trials on stereotactic irradiation of the resection cavity: Both the trial by Mahajan et al. [5] comparing adjuvant local irradiation to observation, and the trial by Brown et al. [6] that compared adjuvant local treatment to WBRT, applied SRS. Within the prospective trial by Mahajan et al. 63 patients randomized in the treatment arm were irradiated with 1 × 12–16 Gy prescribed on the 50% isodose line, applying a 1 mm safety margin. Irradiation was carried out with a Leksell Gamma Knife, using a stereotactic head frame for patient positioning. Patients with a  maximum of three resected metastases with a cavity size of ≤ 4 cm were included in the trial. Reporting no event of radiation necrosis, local control (LC) of the irradiated resection cavity at 12 months was 72%, which was significantly superior to observation alone. Brown et al. included patients with one resected brain metastasis and a maximum of four brain metastases in their prospective trail. The 98 patients randomized into the SRS arm received 1 × 15–20 Gy with a safety margin of 2 mm. The irradiation dose was prescribed to the highest isodose line encompassing the planning target volume (PTV). Maximum cavity diameter was 5 cm. At 12 months after SRS, LC and radionecrosis rate were 61% and 4%, respectively. The trial was able to show that WBRT significantly yields more cognitive deterioration without improving overall survival compared to SRS. For SRS, safety margins are generally smaller than for fractionated regimens, which may likely be responsible for the relatively higher local failure rate in the single-dose trials. For reproducibility, an approach recommending standardized contouring of the surgical cavity for stereotactic radiosurgery has been published recently [12].

However, the published treatment regimens of our own institution by Specht et al. [13], applying 35 Gy in 7 fractions to the 95–100% isodose line, were demonstrated to be not only feasible and safe, but also superior in terms of LC compared to the results of the beforementioned prospective trials, reporting a 1-year LC of 88%. A favorable LC rate after HFSRT was also shown in a multicenter analysis by Combs et al. [14], reporting a crude LC rate of 80.5% after adjuvant radiotherapy to the resection cavity with a median dose of 35 Gy (range 20–42 Gy) in 7 fractions (range 4–14). The hypothesis of superiority of HFSRT is further supported by the results of a recently published international multicenter analysis by Eitz et al. [15] demonstrating a 1-year LC rate of 84% after irradiation with a median total dose of 30 Gy (range 18–35 Gy) and a dose per fraction of 6 Gy (range 5–10.7 Gy). So far, it exists only one broad meta-analysis that revealed significantly improved LC rates after HFSRT compared to SRS [16] (pooled rate of LC at 12 months of 87.3% vs 80.0%, *p* = 0.021). The observed superiority of HFSRT in terms of LC may be due to fractionation, differences in target volumes i.e., safety margins, or other. However, which treatment is superior can only be clarified within a prospective randomized trial. We therefore designed the SATURNUS study comparing both treatment regimens in a standardized and prospective way.

## Methods/Design

### Aim of the trial

Based on our own institutional data [13] and a recently published meta-analysis [16], we hypothesize that LC after HFSRT is superior compared to LC after SRS. With this study, we seek to prove the superiority of HFSRT in terms of LC. To the best of our knowledge, the SATURNUS study is the only randomized phase III study comparing different techniques of postoperative stereotactic radiotherapy after resection of brain metastases adequately powered to detect a superiority of HFSRT regarding LC.

### Trial registration

The study was retrospectively registered with ClinicalTrials.gov, number NCT05160818, on December 16, 2021. The trial registry record is available on https://clinicaltrials.gov/study/NCT05160818. The presented protocol refers to version V1.3 from March 21, 2021. Important protocol modifications, if applicable, will be published in the study’s entry on ClinicalTrials.gov.

### Trial population

Patients with up to three resected brain metastases and possibly further brain metastases for which there is no indication for surgery.

### Primary endpoint

Rate of LC at the resected site(s) at 12 months

### Secondary endpoints

Rate of LC at all treated site(s) at 12 monthsRate of locoregional control (LRC) at 12 monthsOverall survival (OS)Salvage-free survivalNumber and kind of intracranial salvage treatmentsRate of pseudoprogressionIrradiation-related toxicity according to CTCAE v4.03, especially rate of radionecrosisQuality of life according to EORTC QLQ-C30 and EORTC QLQ-B20Time to loss of independence defined as decrease in Barthel index by > 20 points

### Inclusion criteria

Histologically confirmed solid tumor diseaseOne to three resected brain metastasesConsent to perform adjuvant irradiation by an interdisciplinary tumor boardCompleted wound healingResection within the last six weeks at the time of study inclusionDiameter of the resection cavity ≤ 4 cm (on Planning MRI)Age ≥ 18 yearsKarnofsky Performance Score (KPS) ≥ 60%Adequate contraceptive measures for fertile women / menWritten informed consent (must be available before enrolment in the trial)

### Exclusion criteria

Contraindication for repetitive contrast enhanced MRILeptomeningeal diseaseSmall cell histology, hematological malignancies and / or germ cell malignanciesPrevious irradiation of the brainPregnant and lactating womenInability to understand the character and consequences of the studyWithdrawal of consent

### Trial design

The trial is designed as a prospective, randomized, controlled, monocentric phase III trial. It is conducted at the academic hospital Klinikum rechts der Isar of the Technical University of Munich, Germany. A flow chart of the study is provided in Fig. 1. Patients fulfilling the above criteria are considered for study participation and participants are randomly 1:1 allocated to either adjuvant HFSRT (6 – 7 × 5 Gy i.e., 30 Gy/6 fractions or 35 Gy/7fractions; Arm A) or SRS (1 × 12–20 Gy; Arm B). In case a higher dose is needed for adequate tumor control (at the discretion of the treating physician), the maximum allowed dose depends on the cavity diameter and does equivalate the findings of the RTOG 90–05 trial (24 Gy, 18 Gy, and 15 Gy for tumors ≤ 20 mm, 21–30 mm, and 31–40 mm in maximum diameter) [17]. Unresected brain metastases, if present, are treated with SRS (1 × 14 – 22 Gy, prescribed to the surrounding isodose). The affiliation to the treatment arm will not be blinded to anyone except the study neuroradiologist.

**Fig. 1 Fig1:**
[figure not shown]
Flow chart of the SATURNUS/NCT05160818 trial

### Randomization

Patients are randomized 1:1 into the two treatment arms using a randomization list generated with Randomizer, a randomization service for clinical trials, available free of charge at https://randomizer.at. Permuted block randomization with a block size of eight is applied. Sealed envelopes are used and opened by the responsible study nurse or study physician. Assignment to a therapy device is not subject to randomization but is analogous to clinical practice.

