### Statistical considerations and sample size calculation

The underlying null hypothesis of this study is that there is no difference in terms of LC between HFSRT and SRS. The aim of the study is to provide evidence that allows to refute the null hypothesis with a certainty of at least 95% (95% CI), so that the alternative hypothesis can be considered valid. The alternative hypothesis is that HFSRT is superior to SRS in terms of LC. The underlying data for case number calculation are the prospective trials by Mahajan et al. [5] and Brown et al. [6] for SRS (pooled mean LC rate of 66% at 12 months) and our own institutional retrospective data for HFSRT [13] (mean LC rate of 88% at 12 months). The sample size calculation was performed with a two group Chi-squared test of equal proportions (odds ratio = 1). The test significance level (α) was set to 0.05. Allocating an equal number of patients to both treatment arms, 114 patients are needed to detect a superiority of HFSRT with a power of at least 80%. We estimated a dropout rate of 10%, resulting in a total number of 126 patients, and a monthly accrual of three patients. Patients will be randomized 1:1 in the two different treatment arms. Logistic regression analysis will be used to perform predefined subgroup analyses with respect to the primary endpoint.

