### Subgroup analyses

Apart from fractionation schemes, there exist other parameters that might influence LC after RC irradiation. To evaluate possible further influencing factors, the PubMed database (https://pubmed.ncbi.nlm.nih.gov) was searched for the combined criteria "brain metastases", "resection cavity irradiation" and "local control". The literature search yielded 137 articles. After abstract review, 13 articles remained that appeared suitable to deliver relevant information, all retrospective in nature. There is no parameter that has consistently been demonstrated as a significant influencing factor on LC. However, those factors that showed a significant influence of LC in at least one dataset have been included as stratification factors for subgroup analyses. Subgroup analyses will be carried out using logistic regression analysis. The influencing factors identified are listed below, together with the supporting literature:

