### Recruitment and trial duration

Recruitment of patients started in May 2021. The first patient was enrolled on 05/06/2021. The trial is currently recruiting. After completion of the recruitment phase, a minimum FU period of 12 months is planned. Estimating a recruitment rate of three patients per month, the projected time to complete the study will be 4.5 years.

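### One fixed, published block size of eight in an open-label single-centre trial makes about one allocation in five deducible in advance

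*Protocol article*

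**What the plan says.** The Randomization section of the protocol article gives a 1:1 list from a randomisation service and one block size: "Permuted block randomization with a block size of eight is applied". On release it says: "Sealed envelopes are used and opened by the responsible study nurse or study physician".

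Three statements elsewhere bear on this:

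- Trial design: "The trial is designed as a prospective, randomized, controlled, monocentric phase III trial".
- Trial design, on blinding: "The affiliation to the treatment arm will not be blinded to anyone except the study neuroradiologist".
- Recruitment and trial duration: "The trial is currently recruiting".

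No randomisation strata are named. The Subgroup analyses section lists factors that "have been included as stratification factors for subgroup analyses", which concerns the analysis and not the allocation. One running list for the whole trial is therefore the natural reading. The article does not mention varying block sizes or keeping the block size from recruiting staff.

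**The concern.** Permuted blocks protect against foreknowledge only while the block boundaries cannot be inferred. Here one site sees the whole sequence, and each arm is plain once treatment starts (one fraction against six or seven). The block length is constant and now public. When four patients in a block have gone to one arm, the rest of that block is determined.

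Foreknowledge would let a patient be offered the trial sooner, later or not at all according to the next arm. Two traits the article lists as possible influences on local control, cavity size and residual tumour, are read from the planning MRI. Cavity diameter on that scan is also an eligibility criterion. The site holds a stated hypothesis in favour of HFSRT, which implies no misconduct but is the usual reason for strong concealment.

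The safeguards in the article work elsewhere. Intention-to-treat analysis deals with departures after randomisation, and blinded image reading limits assessment bias. Neither corrects selection before randomisation.

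**Working it through.** **Inputs from the article.** Block size 8, 1:1 (four per arm); 126 patients in total, 114 evaluable; local control at 12 months 66% (SRS) and 88% (HFSRT), a difference of 22 points.

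**The plan's own figure.** The article gives no predictability figure. Its sample size does reproduce, which confirms 22 points as the yardstick. With a mean proportion of 0.77, two-sided α of 0.05 and 80% power:

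n per arm = [1.96 × √(2 × 0.77 × 0.23) + 0.842 × √(0.66 × 0.34 + 0.88 × 0.12)]² / 0.22² ≈ 56.3, so 57 per arm and 114 in all (power 80.5%). Then 114 × 1.1 = 125.4, rounded up to 126.

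**Certain allocations, fixed block of 8.** There are C(8,4) = 70 equally likely blocks. An allocation is certain if one arm has already used its four places.

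| Position in block | Chance that it is certain |
|---|---|
| 1–4 | 0 |
| 5 | 2/70 = 2.9% |
| 6 | 10/70 = 14.3% |
| 7 | 30/70 = 42.9% |
| 8 | 70/70 = 100% |

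The sum is 112/70 = 1.6 per block, or 1.6/8 = 20%. The closed form agrees: with m = 4 per arm the fraction is 1/(m + 1) = 1/5.

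Over 126 patients there are 15 full blocks plus 6 places: 15 × 1.6 + 0.029 + 0.143 ≈ 24.2, or 19.2%. Over 114 the figure is 22.4 (19.6%).

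**Guessing.** Always guessing the arm that is behind in the block is right 5.33 times in 8, or 66.6%, against 50% by chance.

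**Possible bias.** Let Δ be the difference in expected local control between patients steered towards HFSRT and those steered towards SRS. The article gives no value, so Δ = 5 to 20 points is an assumption.

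- Only certain allocations used: bias = 0.20 × Δ.
- Steering on a guess at every enrolment: bias = (2 × 0.666 − 1) × Δ = 0.332 × Δ.

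| Δ (assumed) | Certain only | Guess at every enrolment |
|---|---|---|
| 5 | 1.0 | 1.7 |
| 10 | 2.0 | 3.3 |
| 20 | 4.0 | 6.6 |

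**Effect of varying the block size.** This is a simulation of 2,000 trials of 126 patients. The observer knows the set of sizes but not their order. The sets are illustrative.

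| Sizes | Certain allocations of 126 | Best-guess success |
|---|---|---|
| 8 only | 24.2 (19.2%) | 66.3% |
| 4, 6, 8 | 2.8 (2.2%) | 67.9% |
| 6, 8, 10 | 2.0 (1.6%) | 66.3% |

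Varying the sizes removes most of the certainty and almost none of the advantage from guessing.

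**The case against.** The strongest reply is that a weakness in design is not evidence of bias. A reader might infer that a fifth of allocations were in fact known to staff. The article does not support that. It does not say that recruiting staff knew the block size before publication, kept a tally or deferred anyone. The allocations are deducible, not known.

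A reader might also take one bias figure, such as 3.3 points or 15% of the planned effect, as the expected bias. That figure needs a 10-point contrast, which has no source in the article, and successful steering on a guess at every enrolment. Only a range under stated assumptions can be defended.

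A third tempting reading is that the envelopes are insecure, or are opened before the patient is registered. The article says who opens them and no more. Opacity, numbering and the order of registration and opening may be in the full protocol, which is not shown. These details would not, however, stop prediction from a known block size.

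Some mitigation is real. Eight is better than a smaller fixed block: four gives 33% certain allocations and six gives 25%. At three patients a month one place lasts about ten days, and resection must lie within six weeks of inclusion. Deferral is therefore limited, though not excluded. Cavity size and extent of resection are predefined subgroup factors, so gross imbalance could be seen. None of this removes the predictability of the list.

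**Conclusion.** The point stands as an avoidable weakness in allocation concealment. Someone at the site with the block size and a tally can deduce about 20% of allocations, about 24 of 126. This assumes a single unstratified list. With strata, the 20% would apply to each full block within a stratum, and incomplete blocks would lower it slightly.

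Under the assumed contrast of 5 to 20 points, exploiting only the certain allocations would bias the comparison by about 1 to 4 points. Guessing at every enrolment would give about 1.7 to 6.6 points. Against 22 points, neither would by itself account for the planned effect, but either could distort a smaller observed difference. The article gives no sign that such steering has occurred, and the weakness does not invalidate the trial.

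**What to change.** For patients still to be randomised, generate a new list with randomly varying block sizes, and disclose neither the sizes nor their order to recruiting staff. Preferably, release each allocation through the randomisation service already used, after the patient has been registered, in place of envelopes on site. If the full protocol already requires registration first, the trial report should say so.

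The amendment should state what this achieves: certain allocations fall from about 19% to about 2% (illustrative sizes 4, 6 and 8), while best-guess success stays near 66–68%.

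The cost is a small amendment and two lists to document. The service is described as free of charge, and no treatment, endpoint or sample size changes. A comparison of results before and after the change would be descriptive only, because the number of remaining patients is not stated. If recruitment has since closed, what remains is a descriptive check of whether baseline cavity size and residual tumour differ with the arm that could have been predicted.

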### Treatment devices, patient positioning and image guidance

Irradiation is carried out with a Leksell Gamma Knife (Elekta, Stockholm, Sweden) or a Linear Accelerator dedicated for high-precision radiotherapy. For SRS at the Gamma Knife, two methods of patient positioning are available: stereotactic mask or stereotactic frame. In an informed consent procedure, the patient chooses the fixation method himself/herself. For HFSRT at the Gamma Knife, only mask fixation is offered due to the reproducibility on the different treatment days. For image guidance, a stereotactic ConeBeam-CT is used. Besides, during irradiation, an infrared tracking system (High Definition Motion Management, HDMM, Elekta, Stockholm, Sweden) is used. For irradiation at the Linear Accelerator, patient positioning will be carried out using a thermoplastic mask system as otherwise technically not feasible. Precise dose application is ensured with the ExacTrac system (X-ray-based positioning system, Brainlab, Germany).

### Dose prescription

Arm A HFSRT: 6 – 7 × 5 Gy prescribed to the surrounding isodoseRationale: Dose regimen is analogous to the own institutional data by Specht et al. [13] yielding excellent local control rates after adjuvant stereotactic irradiation with 7 x 5 Gy on which the sample size calculation is based (see below). It has been shown that 6 x 5 Gy and 7 x 5 Gy lead to comparable tumor control rates in adjuvant stereotactic irradiation of the resection cavity [14], and therefore dose de-escalation to 6 x 5 Gy may be allowed, if desired/needed for protection of structures at riskArm B SRS: 1 × 12-20 Gy prescribed to the surrounding isodose, depending on cavity size and proximity to structures at risk.Rationale: Dose regimen for SRS are analogous to the dose regimen applied in the phase III trials by Mahajan et al. [5] and Brown et al. [6], on which the sample size calculation is based (see below). Mahajan et al. applied SRS with 1 x 12-16 Gy, whereas Brown et al. delivered postoperative SRS with 1 x 15-20 Gy.In case a higher dose is needed for adequate tumor control (at the discretion of the treating physician), the maximum allowed dose depends on the cavity diameter and does equivalate the findings of the RTOG 90-05 trial (24 Gy, 18 Gy, and 15 Gy for tumors ≤ 20 mm, 21-30 mm, and 31-40 mm in maximum diameter, respectively) [18]Unresected brain metastases, if present, are treated with SRS: 1 × 14 – 22 Gy prescribed to the surrounding isodose. In individual cases (e.g., metastasis near the brain stem), a fractionated approach with, for example, 6 × 5 Gy may be necessary.

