### Dose constraints

Structures at risk such as the brain stem, optic nerves, chiasm, and spinal cord will be contoured. Dose constraints of normal tissue will be respected according to the Quantitative Analyses of Normal Tissue Effects in the Clinic (QUANTEC) recommendation [19]. Radiotolerance of adjoining structures at risk can be limiting to dose prescription and can in certain cases require a slight reduction of the abovementioned dose regimen. For healthy tissue special consideration will be given to the healthy brain, which is being defined as structure at risk (healthy brain = whole brain – sum of all PTVs).

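### For resection cavities above 20 mm the SRS arm has two conflicting upper dose limits (20 Gy against 18 or 15 Gy), and the text does not say which prevails

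*Protocol article*

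**What the plan says.** In the protocol article, Dose prescription gives Arm B as "1 × 12-20 Gy prescribed to the surrounding isodose, depending on cavity size and proximity to structures at risk". It does not say which part of that range belongs to which cavity size. The same section continues: "In case a higher dose is needed for adequate tumor control (at the discretion of the treating physician), the maximum allowed dose depends" on cavity diameter, and lists "24 Gy, 18 Gy, and 15 Gy for tumors ≤ 20 mm, 21-30 mm, and 31-40 mm in maximum diameter, respectively".

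Trial design states the same 12 to 20 Gy range and then the same rule: "the maximum allowed dose depends on the cavity diameter", with "24 Gy, 18 Gy, and 15 Gy for tumors ≤ 20 mm, 21–30 mm, and 31–40 mm in maximum diameter". The Methods part of the Abstract repeats the range alone.

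Under Inclusion criteria a cavity may measure up to 4 cm on the planning MRI, so all three diameter classes can be enrolled. Subgroup analyses sets a dose subgroup split at a margin dose of 48 Gy BED10.

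**The concern.** The diameter limits come in through a condition: they apply when more dose is wanted. Read in sequence, the ordinary range comes first and the exception for going above it second. An upper limit on an exception of that kind should exceed the ordinary maximum. In two of the three size classes it is lower.

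Two physicians can follow this text in good faith and work to different limits for the same cavity. One treats the diameter figure as a cap on any SRS dose. The other treats it as relevant only once 20 Gy is to be exceeded.

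Two things are at stake:

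- **Safety.** A maximum single-fraction dose to the brain protects patients and should have one value per situation. Under Analysis plan, a significant difference between arms in therapy-related SAEs closes the trial, so the limit applied in Arm B can bear on that decision.
- **The dose subgroup.** The Discussion accepts that the dose corridors are broad, especially for SRS, and relies on predefined subgroup analyses by dose and cavity size to deal with this. Which dose groups a large SRS cavity can enter depends on which limit is applied.

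**Working it through.** **1. The plan's own figure, to see whether it is touched.** Inputs from Statistical considerations and sample size calculation: 66% against 88% local control, alpha 0.05, power 80%, equal allocation, chi-squared test. Two-sided testing is assumed, because the sidedness is not stated.

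n per arm = [1.96 × √(2 × 0.77 × 0.23) + 0.8416 × √(0.66 × 0.34 + 0.88 × 0.12)]² / 0.22²
= (1.1665 + 0.4835)² / 0.0484 = 56.2, rounded up to 57. The total is 114, as stated. Dose does not enter the formula.

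**2. Diameter limit minus the top of the ordinary range (20 Gy).**

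| Cavity diameter | Diameter limit | Difference from 20 Gy |
|---|---|---|
| up to 20 mm | 24 Gy | 24 − 20 = +4 Gy |
| 21–30 mm | 18 Gy | 18 − 20 = −2 Gy |
| 31–40 mm | 15 Gy | 15 − 20 = −5 Gy |

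Only the first class fits a rule about exceeding the range. The doses in dispute are those above 18 and up to 20 Gy in the second class, and those above 15 and up to 20 Gy in the third. At 31–40 mm the higher maximum exceeds the lower by one third (20/15 = 1.33).

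**3. The limits on the scale of the dose subgroup.** For one fraction of D Gy, BED10 = D × (1 + D/10).

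- 12 Gy: 12 × 2.2 = 26.4
- 15 Gy: 15 × 2.5 = 37.5
- 18 Gy: 18 × 2.8 = 50.4
- 20 Gy: 20 × 3.0 = 60.0

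The cut of 48 solves D² + 10D − 480 = 0, so D = −5 + √505 ≈ 17.5 Gy.

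- **31–40 mm:** the maxima are 37.5 or 60.0, on opposite sides of 48. If the diameter limit caps every dose, all SRS cavities in this class fall below the cut, and dose group and size class cannot be separated there within Arm B. If it does not, such cavities can fall on either side.
- **21–30 mm:** the maxima are 50.4 or 60.0, both above 48. Either reading allows doses on both sides of the cut.

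**4. Search for a rule of precedence.** Neither Trial design nor Dose prescription says that the diameter figure overrides the range, or the reverse. The clause "depending on cavity size and proximity to structures at risk" says that size matters but attaches no doses to sizes.

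**The case against.** The best defence is that 12 to 20 Gy is an envelope across all sizes. The range is itself said to depend on cavity size, and the diameter figures are called maxima. On that view, higher means higher than the dose otherwise chosen for that cavity, and the diameter figure is always the cap. This is a workable reading and may be what was meant. It is not what the text states. In the smallest class the limit of 24 Gy goes beyond 20 Gy, so there the sentence does extend the range; the word would have to carry a different sense in the other two classes. No size bands are given for the ordinary range that would settle it.

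It can also be said that an article condenses the full protocol, and that the authors acknowledge wide dose corridors. The first would answer a complaint about missing detail, but here two stated limits disagree, in two sections. The second concerns intended discretion within a range, not which maximum bounds it.

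Other parts of the defence stand, and they limit the point:

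- A reader might infer that the dose limit is undefined. It is not: there are two definite limits in conflict.
- A reader might infer doubt about which arm the limits govern. In Trial design the sentence follows directly on Arm B, and in Dose prescription it sits within the Arm B text. The Arm A totals of 30 and 35 Gy exceed all three limits.
- A reader might count the Dose constraints section as part of the conflict, since radiotolerance "can in certain cases require a slight reduction of the abovementioned dose regimen". That concerns reductions near structures at risk and sets no upper limit by diameter.
- A reader might infer that the SRS comparator no longer matches the 66% planning rate. The two source trials used 12–16 and 15–20 Gy, so 15, 18 and 20 Gy all lie within the doses behind that rate.

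**Conclusion.** The contradiction holds. In two of three eligible diameter classes the SRS arm has two permitted maxima, 20 against 18 Gy and 20 against 15 Gy, with no statement of which governs. It is a patient-safety ambiguity and warrants correction. Its analytical reach is narrower: the maxima fall on opposite sides of the 48 Gy BED10 cut only at 31–40 mm.

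These figures compare permitted maxima, not delivered doses. The ordinary range already spans BED10 26.4 to 60 and so straddles the cut by itself. The article gives neither the share of patients with cavities above 20 mm nor the reading used in practice, so it does not support a claim that anyone was treated outside an intended limit or that the comparison cannot be interpreted. The sample size of 114 and the 66% planning rate stand. No view is taken on which limit is right.

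**What to change.** Reconcile the ordinary SRS range and the diameter-based maxima in Trial design and Dose prescription, and adjust the range repeated in the Abstract if needed, so that the text states for each diameter class which limit governs. The figure itself is for the clinical team. For patients already treated, record which reading was applied, so that the analyses by dose and cavity size can be interpreted.

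The cost is a clarifying amendment and a check of existing treatment records. It needs no additional patients, visits or procedures, and the sample size calculation does not change. The article describes the trial as still recruiting, so on that account the clarification can also serve patients yet to be treated.
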